### Blinding

2.7

Participants and intervention delivery facilitators cannot be blinded to group allocation. However, assessors conducting the outcome measures and coders scoring the video-recorded/audio-recorded observations will be blinded to group allocation.

### Interventions

2.8

Children allocated in Group 1 (Clinical Monitoring Group) won't perform any treatment, but only clinical evaluations, at the defined time points. On the contrary, children of Groups 2 and 3 will perform training according to the following guidelines.

#### Active monitoring (AM) group

2.8.1

Children of this group (Group 2) will be enrolled in a 90-minute session once a month for 6 months. Sessions will be performed by an expert neuro and psychomotor therapist for developmental age supported by a child neuropsychiatrist or psychologist. A parent will always be present and actively involved in the intervention. During these sessions, the aims will be (i) to monitor and discuss the achievement of developmental milestones in sensory-motor, cognitive and socio-communication domains through clinical observation; (ii) to share with caregivers some strategies and activities appropriate for the age of the child to promote the achievement of developmental milestones and the active participation of the child in everyday activities; and (iii) to discuss with parents’ needs, problems and concerns about the development of the child and their parent-child relationship to provide educational advice.

#### Early intervention (EI) group

2.8.2

Children of this group (Group 3) will be enrolled in a 90 min parent-coaching session once a week for six months with an expert neuro and psychomotor therapist for developmental age supported by a child neuropsychiatrist or psychologist. A parent (preferably the mother) will always be present and actively involved in the intervention. The intervention is individualised and tailored to each child's needs, and clinicians will work with parents to identify ways to incorporate objectives into daily life. It will be carried out using a multidimensional, naturalistic and family-centered approach. We will consider promoting postural-motor, socio-communicative and cognitive skills, always considering the sensory profiles of each child. The key elements of the EI protocol are (i) the stimulation of the neurodevelopment of the child in a harmonious way, considering all developmental domains; (ii) the involvement of the caregivers to facilitate social reciprocity and to coach them in understanding the communication signals of their child and to interact with their child in enjoyable, responsive, and non-intrusive modalities; and (iii) the support parents in their parent experience and their feelings about their interaction with their child. During the sessions, the parent's involvement, according to a parent-coaching approach, can guarantee sharing goals and strategies to stimulate the child at home. Parents will also be encouraged to engage in regular stimulation at home, with a goal dose of 20–30 min per day, according to their child's availability. It will be suggested that parents record short home videos each week during play activities to observe and discuss what happened at home. Sessions may also contain a small psychoeducation component on common early parenting challenges such as sleep, crying and feeding.

An explanation of the structures of the AM and EI sessions is reported in Table 1.

**Table 1 T1:** General features and goals of active monitoring (AM) and early intervention (EI) of the ERI-SIBS project.

Component	Active monitoring	Early intervention
Involved professionals	Neuropsychomotor Therapist for Developmental Age + Child Neuropsychiatrist/Child Psychologist	Neuropsychomotor Therapist for Developmental Age + Child Neuropsychiatrist/Child Psychologist
Frequency	1 session of 1,5 h every month	1 session of 1,5 h every week
Role of parents	At least one parent is active in the sessions	At least one parent (preferably the mother) is active in sessions
Goal 1	To provide information about child development and to monitor the achievement of the most important developmental milestones in the child	To stimulate child development in all domains (sensory-motor, cognitive, and social) and to coach the parents in understanding and adequately responding to the communication signals of their child
Goal 2	To share with parents some strategies and activities appropriate for the age of their child for promoting development	To share and implement with parents progressively new strategies and activities for promoting a greater motor and communicative initiative in the child
Goal 3	To discuss with parent's needs, problems, and concerns about the development of the child and their parent-child relationship and to provide educational advice	To support parents in their parent experience and on their feelings about their interaction with their child, to reach together the best strategy for promoting parent-child relationship
Strategies and modalities	Counselling to share and show activities, objects, and strategies to propose to the child during the interaction; discussion and active listening with parents.	Parent-coaching; neuro-psychomotor stimulation of the child; discussion and video-feedback; psychological counselling and active listening for parents.
Instruction for parents at home	Implement strategies and activities during the everyday activities of the child and family.	Stimulations during free play sessions at home, at least for 20–30 min per day; implement strategies and activities also during the everyday activities of the child and family.

### Fidelity

2.9

The intervention will be carried out by a neuro- and psychomotor therapist for the developmental age, and it will also be supported by a child neuropsychiatrist or psychologist who is an expert in early intervention. The study clinicians are experienced in working with families of children with early neurodevelopmental disabilities. Clinicians will meet every week to provide peer clinical supervision within the context of a multidisciplinary team. All the clinicians will follow the shared protocol. However, some differences in the specific objectives and therapeutic strategies will be based on every child's individual functioning and every family's needs. All the intervention sessions (Groups 2 and 3) will be videotaped and stored on a device owned by the principal investigator. This permits better supervision from the multidisciplinary team.

### Patient and public involvement

2.10

Preliminary feedback was collected from consumers (parents of children with different developmental disabilities not recruited for this project) on the protocol, the study forms, and the intervention. Consumer feedback was positive, with some changes to the wording made following the input.

### Study procedures

2.11

Researchers will contact interested parents to assess eligibility and provide detailed study information. Parents will provide written consent before completing baseline assessments (T0), and based on the scores from the primary outcome measures, children will be assigned to the correct group. Infants with no signs of concern (scores at the Griffiths-3 and CSBS-ITC in the normal range), which are siblings of TD children, will be allocated to Group 1 (CM); infants with no signs of concern (scores at the Griffiths-3 and CSBS-ITC in the normal range) which are siblings of ASD children will be allocated to Group 2 (AM); infants with a quotient score below 85 using Griffiths-3 and at least one score above the “concern” cut-off using the CSBS-ITC will be allocated to Group 3 (EI). Families allocated to Groups 2 and 3 will start the intervention within one month of the baseline assessment. Families allocated to Group 1 will perform only the evaluations at different time points. Assessments will be conducted at baseline (T0), which will be when the parents give their consent and within the eight months of life of the child, after six months from the start of the intervention (T1) and after 12 months from the start of the intervention (T2). During the recruitment phase, the study's importance in developing specific guidelines for children at risk of neurodevelopmental disorders will be explained in order to improve adherence to the methodology. Participants may withdraw from the study for any reason at any time.

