#### Primary outcome

1.1.1

**H1:** The main hypothesis of this study is that early parent-mediated intervention in children at risk for neurodevelopmental disorders can be implemented in routine care, positively impacting early sensory-motor and socio-communicative developmental trajectories and reducing the developmental gap in children with signs of concern. For this first aim, we will use standardised, age-appropriate, and sensitive tools to define the presence of early signs suggestive of neurodevelopmental disorders and to monitor their developmental trajectories over time.

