##### Main outcome measures

2.5.1.1

•Early Social Communication Scale (Échelle de la Communication Sociale Précoce, Italian adaptation, ECSP-I): The ECSP-I is a structured assessment to measure individual differences in nonverbal communication skills in children from 3 to 30 months of age. The administration requires 15–20 min and includes the presentation of approximately 23 standardised situations that provide opportunities for social communication (24). The ECSP-I demonstrated strong reliability and both construct and discriminant validity.•Griffiths Scales of Child Development, 3rd Edition (Griffiths-3): Griffiths-3 is the gold standard for providing an overall measure of a child's development (0–6 years); it permits the definition of an individual profile of the child's strengths and needs across five areas: foundations of learning, language and communication, eye-hand coordination, personal-social-emotional, and gross motor (25).•The Communication and Symbolic Behaviour Scales—Infant-Toddler Checklist (CSBS-IT-C) (26) is a developmental screening tool to measure 7 language predictors in children aged 6–24 months. The questions of the checklist may be presented in an interview format with adequate explanations to clarify what is being asked. It takes approximately 5–10 min to complete and permits the detection of signs of concern for ASD in infants and toddlers.•Satisfaction Survey: The parents of children in Groups 2 and 3 will be asked to anonymously complete a survey (created *ad hoc* for this project) immediately after the intervention (T1) to assess their satisfaction with the services provided. The questionnaire took 5 min to complete.

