### Statistical analysis

2.13

Analysis (using STATA or SPSS 28.00) will follow standard methods for trials using comparisons between the three groups. First, a study of the maturation trajectories of the infants will be carried out, with a description of the pre-post intervention changes in the tests carried out. Second, quantitative evaluations of joint attention data and molecular markers will be performed, detected, and described through the mean and standard deviation in the case of a Gaussian distribution of variables or the median and interquartile range in the case of a non-Gaussian distribution. The normality of distributions will be assessed by applying the Shapiro‒Wilk test. For categorical variables, absolute frequencies and percentages will be reported. Genetic analysis of intrafamilial allelic inheritance will be conducted by AFBAC (Affected Family-Based Controls) (55) and TDT (Transmission Disequilibrium Test) (56). The immunological parameters obtained from the groups of ASD children and TD children will be analysed using a nonparametric Mann‒Whitney test that will allow the identification of specific immunological biomarkers of ASD-associated neuroinflammation. Moreover, clinical parameters will be correlated with immunological biomarkers characteristic of ASD children. Finally, epigenetic analysis will allow us to define a panel of microRNAs that can differentiate between ASD children and children with typical development. Using computer algorithms, the potential targets, pathways, and biological functions deregulated by this group of miRNAs will be analysed. These data will also be analysed concerning the clinical parameters evaluated in the study and the genetic and inflammatory characteristics of the subjects studied.

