## Discussion

3

This study aims to provide evidence on the feasibility and efficacy of an innovative and early intervention program for infants at risk of developing neurodevelopmental disorders. In this way, new findings and insights could set the basis for the future development of guidelines on managing early support and intervention for at-risk families, both in the presence and absence of specific risk signs. In fact, evidence suggests that this early and preemptive approach may substantially impact the quality of life for the families involved, reducing parental stress and improving parents’ sense of competence in their role (15, 17). In addition, from an economic standpoint, early diagnosis and intervention can lead to better developmental outcomes, which can result in a decreased need for therapies (such as psychomotor, speech, and physical therapies) and special needs services later in life, thus resulting in improved cost-effectiveness for the health care system in the long run, as already demonstrated (57). Moreover, the approach of the ERI-SIBS program is designed to include in the Italian national health system the more recent scientific literature concerning early intervention for children with neurodevelopmental disorders (58). These are the implementation of training-based interventions harnessing experience-dependent plasticity, the use of environmental enrichment's paradigm for promoting voluntary, self-initiated actions and learning, and the promotion of parent-child interactions, fostering a sense of self-competence and autonomy, a better generalization of child's learnings and the promotion of a secure bonding. Our investigation could contribute to the debate on the intensity and duration of intervention for the developmental domains of young ASD children. In fact, in a recent meta-analysis, Sandbank et al. (59) reported little robust evidence supporting the provision of intensive interventions for this population. Finally, the contribution of biomolecular, genetic, and epigenetic testing, as well as the use of technologies to collect quantitative data on joint attention and early social responses, confers a particular and innovative role to this project: it could allow the collection of preliminary data for characterising biomarkers to understand better not only the natural developmental trajectories of these children but also to identify eventual changes that can be related to clinical early intervention.

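### Griffiths-3 and CSBS-ITC both allocate infants and serve as main outcomes for H1, so a narrowing gap on them is expected from regression to the mean and cannot be read as an intervention effect

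*Protocol article*

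**What the plan says.** **Allocation (2.11).** At T0, "based on the scores from the primary outcome measures, children will be assigned to the correct group". Group 3 consists of "infants with a quotient score below 85 using Griffiths-3 and at least one score above the" CSBS-ITC concern cut-off. Groups 1 and 2 must have "scores at the Griffiths-3 and CSBS-ITC in the normal range", and differ from each other only in whether the older sibling has ASD.

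**Outcomes (2.5.1.1).** ECSP-I, Griffiths-3, CSBS-ITC and a parent satisfaction survey are listed together as main outcome measures, with no priority stated among them. Of Griffiths-3 the section says that "Griffiths-3 is the gold standard for providing an overall measure" of development.

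**Hypothesis (1.1.1).** H1 covers implementation in routine care and better sensory-motor and socio-communicative trajectories, including "reducing the developmental gap in children with signs of concern". The same section uses one set of tools both to define the signs and to follow them over time.

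**Treatment (2.8).** Group 1 has evaluations only, Group 2 monthly sessions and Group 3 weekly sessions. No infant with signs is left untreated or randomised.

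**Analysis (2.13).** Comparisons are between the three groups, and trajectories are studied "with a description of the pre-post intervention changes in the tests carried out".

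**Claims (3).** "This study aims to provide evidence on the feasibility and efficacy of an innovative and early intervention program". Later in the same section: "Our investigation could contribute to the debate on the intensity and duration of intervention".

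**The concern.** Group 3 is chosen for a low score on one occasion, and Groups 1 and 2 for normal scores on the same tests. Part of any extreme infant score is transient. At retest the low group is expected to move up and the normal group slightly down, with or without treatment. H1 predicts the same pattern.

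The three-group comparison does not remove this, because the two drifts go in opposite directions and add. Only a similarly selected group without the intervention could show how much of the change is selection, and there is none. Session frequency is also fixed by group, so it cannot be separated from familial risk and signs.

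What is at stake is the reading of a Group 3 gain on Griffiths-3 or CSBS-ITC. It could be reported as efficacy, or as evidence on intensity, when the design cannot tell it from a selection artefact.

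**Working it through.** **Inputs from the protocol article.** Griffiths-3 cut-off 85 (2.11); 14 per group before drop-out and two-sided alpha 0.01 (2.6).

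**The plan's own figure.** An exact two-sided two-sample t-test with difference 0.8, SD 0.56 and alpha 0.01 reaches 80% power at 14 per group (83.1% at 14, 79.2% at 13). The stated 14 reproduces. That calculation concerns ECSP-I differences at each time point, not change on the allocation tests, so only its n and alpha are used here.

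**Assumptions not in the document.** Quotient mean 100 and SD 15; bivariate normal T0 and T1 scores with correlation r; selection on Griffiths-3 alone; no intervention effect; stable true standing.

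**Step 1, T0 means.** The cut lies at (85 − 100)/15 = −1 SD, with φ(1) = 0.2420 and Φ(−1) = 0.1587.

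- Group 3: 100 − 15 × 0.2420/0.1587 = 77.1
- Groups 1/2: 100 + 15 × 0.2420/0.8413 = 104.3
- Gap at T0: 27.2

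**Step 2, expected retest.** Each group's distance from 100 is multiplied by r. Group 3 rises by 22.9 × (1 − r), Groups 1/2 fall by 4.3 × (1 − r), and the gap shrinks by 27.2 × (1 − r).

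**Step 3, chance of a significant difference in change.** Within-group variance of change is 225 × [(1 − r)² × v + 1 − r²]. Here v is the variance of the truncated standard normal: 0.199 below the cut and 0.630 above it. Averaging the two variances and taking the root gives the SD of change. With 14 per group the noncentrality is (shrinkage/SD) × √7 on 26 df. The rates are for a two-sided test that favours Group 3, against nominal 2.5% and 0.5% in that direction.

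| r | Group 3 rise | Gap shrinkage | SD of change | Noncentrality | Significant at 0.05 | Significant at 0.01 |
|---|---|---|---|---|---|---|
| 0.5 | 11.4 | 13.6 | 13.9 | 2.60 | about 70% | about 44% |
| 0.8 | 4.6 | 5.4 | 9.2 | 1.56 | about 32% | about 13% |
| 0.9 | 2.3 | 2.7 | 6.6 | 1.09 | about 18% | about 6% |

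At r = 1 the shrinkage is zero.

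**Step 4, sensitivity.**

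- Selecting on both tests (assumed CSBS-ITC concern rate 15%, correlation 0.5 with Griffiths-3) makes the effect somewhat larger. The gap goes from 29.8 to 15.0 (r = 0.5), 23.8 (r = 0.8) or 26.8 (r = 0.9).
- A source-population mean of 92 instead of 100 makes it smaller. Group 3 then rises 8.4 points at r = 0.5 and 3.4 at r = 0.8.
- In both cases the gap still shrinks by a fraction of about 1 − r.

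**The case against.** **Certainty.** A reader might infer that an inert programme is bound to show a closing gap. The document does not support that. The expectation assumes that Group 3's true standing is stable, and the Introduction describes these siblings as at increased risk of abnormal trajectories. A true decline could offset the rise. It would hide the artefact, not remove it, and the observed change would still be uninterpretable.

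**Tests not planned.** A reader might take the rejection rates as the trial's false-positive rate. Section 2.13 promises description and names neither a paired test nor a difference-in-change test. The sample size uses alpha 0.01, not 0.05, and compares groups at each time point. A comparison of T1 means alone would not favour Group 3 under the null. The rates are therefore illustrations. The bias in a described mean change remains.

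**ECSP-I.** A reader might conclude that the whole main result rests on the artefact. It does not. ECSP-I is the first-listed main outcome, is the basis of the sample size and has no cut-off in 2.11. H1 also covers implementation in routine care. The problem is confined to Griffiths-3 and CSBS-ITC, but these stand beside ECSP-I with no priority given.

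**A separate analysis plan.** Baseline handling is commonly left to one. That stands as far as analysis detail goes, but no analysis can supply an untreated group with signs.

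**Hedged wording.** The intensity sentence in section 3 says only that the study could contribute. It still points to an inference that a frequency fixed by group cannot support.

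**Conclusion.** The point holds for the two allocation tests. With both used to select Group 3 and both serving as main outcomes for H1, a rise in Group 3 and a narrower gap are expected without any effect whenever the T0-T1 correlation is below 1, unless a true decline offsets them. The design cannot separate this from benefit.

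The firm result is the proportional one: the gap shrinks by about 1 − r, that is 50%, 20% or 10% at r = 0.5, 0.8 or 0.9. The points and rejection rates depend on an assumed mean, SD, correlation and test, none of which the document gives. ECSP-I is exposed only through T0 error shared with the allocation tests, and through the confounding of group with treatment. The efficacy and intensity/duration inferences in section 3 go beyond what the design can show.

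**What to change.** 1. **Section 2.5.1.1.** Name ECSP-I as the measure on which the socio-communicative part of H1 is judged. Keep Griffiths-3 and CSBS-ITC for allocation and descriptive follow-up. Acknowledge that the sensory-motor part of H1 then stays descriptive, since ECSP-I measures nonverbal communication only. Also acknowledge that ECSP-I still carries the group confounding and any T0 error shared with the allocation tests.
2. **Section 2.13.** State that Group 3 change, or narrowing against Groups 1 and 2, on the two allocation tests is not evidence of effect. Report it beside the narrowing expected from regression to the mean over a range of correlations.
3. **Section 3.** Limit the aim to feasibility and description of trajectories. Remove the efficacy and the intensity/duration inferences, because session frequency is fixed by group.

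A comparison of Group 2 with the high-risk infants in Group 3, adjusted for T0 Griffiths-3 and CSBS-ITC, should not be offered as a remedy. Allocation is deterministic on those scores, so the groups do not overlap and the estimate would rest on extrapolation.

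**Cost.** Wording in three sections and one descriptive display from data already collected. The sponsor gives up an efficacy claim, and the sensory-motor part of H1 becomes descriptive.

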### Data collection and management

2.12

The data will be collected, organised, managed, and stored in Research Electronic Data Capture software (REDCap) according to the Italian security, integrity, and confidentiality criteria. The data will be entered into the REDCap database in a potentially individually identifiable format. Once de-identified, the data will be stored in an identifiable format on a secure electronic database protected by the Fondazione Don Gnocchi secure server and accessible only to research team members. The different skills of the staff of the different units involved in the project will be integrated in the best possible way to achieve the desired results. Based on their expertise, different professionals will be coordinated centrally by the neuropsychiatrists to collect several planned measurements and facilitate the adherence and eliciting of information from study participants in a uniform, reproducible manner. The data relating to the project results will be communicated to protect the participants’ privacy. In the case of scientific publications, long-term repositories for anonymised data will be used, which may have open or restricted access criteria to ensure the sustainability of the collected data.

